#### Effect evaluation

The primary outcome measure is length of hospital stay, defined as the number of nights that a patient stayed in hospital after surgery. Secondary outcome measures are length of recovery and guideline adherence. Recovery is defined as the first day after surgery that the patient fulfilled all three discharge criteria: tolerance of food, adequate pain control on oral analgesics, and independency in activities or daily living. The complete ERAS programme, as proposed by the ERAS Society® [2], includes over 20 protocol care elements. Index elements were selected as having a high level of evidence, being readily recordable, or having a direct influence on recovery. Those elements are the following: preadmission counselling, no bowel preparation, carbohydrate load, use of prophylactic antiemetics, removal of nasogastric tube on end of surgery, no peritoneal drainage, start fluids on day 0, start normal food and mobilisation on day 1, use of epidural analgesia, use of laxatives, and urinary catheter removal on day 2. Guideline adherence to the index elements will be registered for all eligible patients during the study period.

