### Sample size

With the support of the DGOG, we expect to include the majority of Dutch hospitals and all patients that will be exposed to major gynaecological surgery during the implementation year. Approximately 100 patients undergo surgery per hospital per year. We do not expect drop outs among patients as informed consent procedures and filling in questionnaires by patients is not needed. The history of adherence to the ERAS protocol in the Netherlands during the implementation year will be described, so this study is in principle not about statistics and sample size calculations. However, it may be still worthwhile to calculate what statistical differences we will be able to assess, taking the perspective that this sample can be seen as an estimate for the future health care or assuming that some hospitals will not participate as expected. The stepped implementation strategy is expected to be superior to the breakthrough strategy in improving perioperative care processes and reducing the length of hospital stay. Anticipating a total adherence of 50 % to the benchmark of length of stay of 5 days or less in the breakthrough hospitals versus 70 % adherence in the stepped implementation hospitals, we would need to randomise seven hospitals per arm, each including at least 60 patients during the whole study period. Sample size computation was based on an estimated intra-class correlation coefficient (ICC) of 0.06 in secondary care, a power level of 80 %, and a significance level (*α*) of 0.05. The intra-class correlation coefficient used to calculate the sample size was based on a study of Campbell et al. [35]. Although this study reported significantly lower ICCs for outcome variables compared to process variables, we have conservatively computed the sample size using the highest applicable ICC of 0.06 for secondary care. Using an inflation factor of 11 % to account for unequal cluster size yields a recruitment target of 67 patients per cluster. It is possible that no clinically relevant differences (<20 %) between arms could be found. In such a case, we expect the stepped implementation programme still to be superior from a financial perspective.

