### Data analysis

#### Effect evaluation

Descriptive statistics (proportions, mean, and median) will be performed for process and outcome data sets. Differences between groups will be evaluated using independent sample *t*-test for numerical variables and chi-square test for categorical variables. Since patients are nested within hospitals, implementation effects will be analysed using linear or logistic mixed-effect model analysis for numerical or binary outcome measures, accounting for a random hospital effect. Since the four implementation periods can be considered as different (time) groups, this time variable will be included as a factor in the regression model. Besides, subgroup analyses will be performed to describe trends in implementation over time in more detail. Non-inferiority comparisons will be presented for outcome measures using 95 % confidence intervals. Two-sided *p* values ≤0.05 will be considered as statistically significant. Statistical analyses will be performed using SPSS® version 22 software (SPSS, Chicago, Illinois, USA).

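### Binary outcomes are tested with a patient-level logistic mixed model on as few as 14 hospitals, with no allowance for few clusters; a large-sample test would have a type I error of about 7-10 %

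*Protocol article*

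**What the plan says.** All references are to the protocol article.

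- **Data analysis, Effect evaluation.** The model is fixed: "implementation effects will be analysed using linear or logistic mixed-effect model analysis for numerical or binary outcome measures, accounting for a random hospital effect". The four three-month periods enter as a factor. Two-sided p "values ≤0.05 will be considered as statistically significant". Non-inferiority comparisons are to be shown with 95 % confidence intervals. SPSS 22 is named. No reference distribution, denominator degrees of freedom or estimation method is given.
- **Sample size.** The calculation is on a binary quantity, the share of patients who meet the 5-day benchmark. It sets 50 % under the breakthrough strategy against 70 % under the stepped strategy. Its other inputs are an "estimated intra-class correlation coefficient (ICC) of 0.06 in secondary care, a power level of 80" per cent, with α set at 0.05. The conclusion is that "we would need to randomise seven hospitals per arm", with a minimum of 60 patients in each hospital (67 after inflation for unequal cluster size).
- **Outcome measures, Effect evaluation.** The primary outcome is the number of nights in hospital after surgery, which is numerical. Adherence is a secondary outcome: "Guideline adherence to the index elements will be registered for all eligible patients during the study period".
- **Design.** Randomisation is by hospital, stratified by tertiary status.

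**The concern.** Information about the arm effect comes from differences between hospitals. With 7 + 7 hospitals there are 14 − 2 = 12 degrees of freedom for that comparison, and adding patients does not raise this number. The ordinary Wald z or likelihood-ratio test of a random-intercept logistic model takes the estimated hospital variance as if it were known. With 14 hospitals that variance is poorly estimated and, under maximum likelihood (ML), biased downwards. Standard errors are then too small and intervals too narrow.

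What is at stake is the test of the 5-day benchmark, on which the trial is sized, and of adherence, a named secondary outcome. A false claim that one strategy is better would be more frequent than the stated 5 %. An interval that is too narrow also makes non-inferiority too easy to claim.

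**Working it through.** **Inputs.** From Sample size: 50 % versus 70 %, ICC 0.06, power 80 %, α 0.05, 7 hospitals per arm, 60 (67) patients each. From Data analysis: random hospital effect, four periods as a factor, two-sided 0.05. Not in the document, so varied: estimation method and reference distribution.

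**1. Reproducing the plan's figure.**
- Two proportions, pooled variance, normal quantiles: 93 patients per arm.
- Design effect: 1 + (60 − 1) × 0.06 = 4.54.
- Hospitals per arm: 93 × 4.54 / 60 = 7.04; power at 7 × 60 is 79.8 %.
- Inflation: 60 × 1.11 = 66.6, rounded to 67.

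The stated seven per arm is therefore what a normal-quantile formula gives. With unpooled variance, power at 7 × 60 is 81.0 % with normal quantiles but 74.0 % with t on 12 df. Eight per arm would give 80.5 % with t on 14 df. The design calculation thus made no allowance for few hospitals. This does not show how the model will be tested.

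**2. Analytic type I error with a z reference, K hospitals, K − 2 df.**
- REML-type variance: P(|t| > 1.96) on K − 2 df.
- ML variance, too small by the factor (K − 2)/K: P(|t| > 1.96 × √((K − 2)/K)). For K = 14 the cut-off is 1.96 × √(12/14) = 1.815.

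| Hospitals | REML-type, z | ML, z |
|---|---|---|
| 14 | 7.4 % | 9.5 % |
| 20 (assumed) | 6.6 % | 7.9 % |
| 25 (assumed) | 6.2 % | 7.3 % |

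The first column also applies to the linear model of nights: 7.4 % at 14 hospitals if z is used.

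The correct multiplier on 12 df is 2.179. An interval built with 1.96 is 1.96/2.179 = 0.90 of its proper width with a REML-type variance, and 1.815/2.179 = 0.83 with an ML variance.

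**3. Null simulation of the logistic model with arm and four periods.** 14 hospitals, 4,000 data sets per scenario, ICC 0.03-0.15, event rate 0.6 or 0.85, equal clusters of 60, 67 or 100 patients or unequal clusters of 30-104. Monte Carlo standard error is about 0.4 points.

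| Fit | z reference | t, 12 df |
|---|---|---|
| ML, adaptive quadrature | 8.9-9.8 % | 6.1-6.8 % |
| REML-type pseudo-likelihood | 6.8-7.6 % | 4.2-5.1 % |

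At an assumed 20 hospitals with z: 7.6 % (ML) and 6.7 % (REML-type).

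**4. Likelihood-ratio test and hospital-level test.** In a separate null simulation (1,500 data sets per setting, clusters of about 67) at ICC 0.06, the likelihood-ratio test rejected in 7.6-8.5 % and ML Wald z in 8.8-10.1 %. A t-test on the 14 hospital proportions rejected in 4.1-5.8 % over all settings, with ICC up to 0.5. A further run at ICC 0.06 gave 9.5 % (ML Wald z), 7.7 % (likelihood ratio) and 5.6 % (hospital-level t-test).

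**The case against.** The strongest objection is that the article never says a large-sample reference will be used. Degrees of freedom are often settled in an analysis plan, and a condensed article may leave them out. This stands in part: the error rate is conditional, and it would be wrong to say that the plan's tests do reject a true null too often. What remains is that the article does fix the model, the threshold and a minimum of 14 hospitals, and the ordinary use of that model exceeds 5 %.

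Second, 14 is a minimum. Most Dutch hospitals are expected to join, and about 2,500 operations a year (Background) divided by about 100 per hospital (Sample size) suggests some 25 hospitals before exclusions. The article states no expected number. More hospitals shrink the excess but do not remove it (step 2).

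Third, a reader might infer a larger problem in three ways, none of which the documents support:
- **That the error reaches 12 %.** Values up to 11.7 % appeared only for ML with Wald z at assumed ICCs of 0.15-0.5, in a simulation not described as including the period factor. With that factor, ICC 0.15 gave 9.2 %. A smaller run (500 data sets per setting) at ICC 0.3-0.5 gave 6.8-9.0 %.
- **That index elements follow hospital policy, lie near 0 % or 100 %, and so have an ICC far above 0.06.** This is plausible for some elements but is an assumption. The article calls 0.06 the highest applicable value for secondary care.
- **That the primary analysis is affected in the same way.** Nights go to the linear model, where the excess arises only with a z reference and disappears with between-hospital degrees of freedom.

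**Conclusion.** The point holds in conditional form. With 14 hospitals and ICC 0.06, a large-sample test of the arm effect on a binary outcome has a type I error of about 7-10 % in place of 5 %: about 9-10 % for ML with Wald z, about 8 % for the likelihood-ratio test, and about 7-7.5 % for a REML-type fit with z. The error is thus roughly 1.4 to 2 times the nominal level, depending on choices the article leaves open. A REML-type fit with 12 df brings it back to about 5 %, so the logistic mixed model itself is not at fault. The figures rest on 14 hospitals, a correct random-intercept model and no arm effect. The matter is a cheap improvement.

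**What to change.** Add one sentence to Data analysis, Effect evaluation: arm effects and their 95 % intervals are based on between-hospital degrees of freedom (Satterthwaite or Kenward-Roger type) with a REML-type fit, for both the linear and the logistic model. For binary outcomes, an equally good alternative is a t-test or regression on hospital-level proportions, or a permutation test that follows the allocation stratified by tertiary status. The logistic mixed model can stay with this correction and need not be reduced to description. A t reference on an ML fit is not enough, since it still gave 6.1-6.8 %.

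The cost is wording only, with no new data. Intervals become slightly wider and power slightly lower, and both then reflect the number of hospitals actually randomised.

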In the Netherlands, the quality improvement model known as the Breakthrough Series [17] is currently adopted as the preferred method for health care improvement on a large scale, despite some serious drawbacks [18]. This structured collaborative learning strategy is designed to help health care organisations attain best practice in a certain field. Systematic evaluations have shown that effectiveness of the breakthrough approach varies and is at the best moderate [19]. Furthermore, breakthrough projects represent substantial investments of time, effort, and funding and are assumed to be expensive [20]. A new approach designed to deliver an optimal effect of implementation efforts at the lowest possible implementation costs is desirable. Based on the underlying assumption that organisations may vary widely in their knowledge, motivation, and capacity to run a quality improvement programme, as prescribed in the meta-evaluation of ten such programmes in the Netherlands [21], a stepped implementation strategy was designed. This strategy aims to tailor the implementation efforts to the variety in needs and local barriers to change. It offers generic low-intensive support for those who smoothly implement the changes and a more tailored and intensive approach for those hospitals having difficulties in making the changes. This differentiation of the implementation activities to preparedness for change is described in various theories on the different phases in a process of change. The Model for Planning Change of Grol describes ten stages, subdivided into awareness, understanding, acceptance, adoption, and integration of the proposed behaviour [22, 23]. This model was used to select the change interventions that will be used in the stepped implementation strategy. Each step leads to a more intensive stage in the process of change. A tailored approach is intensive and seems less suitable for large-scale improvement as it requires local support and elaborative preparatory activities [24, 25]. Evaluation of the process of this implementation effort will provide insight on why and for whom the developed strategy works and improves the understanding of the stepped approach. This will help to define a preferred strategy for nationwide dissemination of best practices.

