### Intervention group

The intervention group will be exposed to the stepped implementation strategy, which consists of four steps of implementation activities. This strategy is built on the assumptions that for some hospitals a generic improvement approach may be sufficient, while for other hospitals a full-blown breakthrough approach or an even more intensive tailored approach may be required. The four levels of intensity will be offered successively, with 3 months in between (Fig. 2).

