### Data collection

Before the start of implementation activities, a baseline audit of process and outcome data will be performed by reviewing medical charts of the first 30 patients treated in 2012. This period was chosen as the ERAS programme was not discussed yet in the DGOG. In case of an insufficient number of patients, the retrospective audit will be completed with patients operated in 2011. Hereafter, from the first day of the start till the end of the project 1 year later, a member of the expert team will monitor process and outcome data for both the intervention and the control group. An electronic database supporting good clinical practice guidelines will be available. Patient characteristics, process indicators, and outcome measures (proportion of patients reaching functional recovery within 3 days and proportion of patients hospitalised for a maximum of 5 days) will be audited for every 3-month period during the 1-year implementation period. The timing of the teaching sessions of the breakthrough project will be synchronous with the timing of the implementation steps (Fig. 2). Although the effectiveness of both strategies will be evaluated and compared every 3 months after every step or teaching session, the main goal of the study is to compare effectiveness at the end of the project using all patients collected during the year. Costs for the two implementation strategies will be calculated from hours and tariffs for the strategy delivery team (CBO expert, subject matter experts) as well as all costs for surgeons, anaesthetists, and nurses attending implementation-related activities, including time, travel, and conference expenses. Furthermore, the costs of materials will be calculated. Additional costs of the audit database will be calculated as well, as this is an essential part of the implementation strategies. Standardised forms will be developed for the measurement of activities, materials, and expenses associated with implementation [34]. Those forms will be filled in by members of the implementation team at each site and will provide information for the economic and process evaluation of the quality mprovement. Qualitative data regarding the process evaluation will be derived from extensive notes of all contacts with each hospital and during the educational sessions. Minutes will be taken by at least two members of the expert or local implementation team.

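### With one random hospital effect and no hospital-by-period term, pooled-model p-values for change across quarters can be too small; the year-long arm comparison is not affected

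*Protocol article*

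**What the plan says.** Under Data analysis, Effect evaluation, the article specifies linear or logistic mixed models "accounting for a random hospital effect". On the four quarters it says that "this time variable will be included as a factor in the regression model". It adds that "subgroup analyses will be performed to describe trends in implementation over time in more detail", and sets two-sided significance at 0.05. It names no random hospital-by-period effect, no random time slope and no arm-by-period term.

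Under Data collection, "effectiveness of both strategies will be evaluated and compared every 3 months after every step or teaching session", but "the main goal of the study is to compare effectiveness at the end of the project using all patients collected during the year". The economic analysis section uses the three-monthly results to judge up to which level of intensity the activities pay off.

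On differences between hospitals, the Background states that "organisations may vary widely in their knowledge, motivation, and capacity to run a quality improvement programme". The Intervention group section takes as its premise that hospitals differ in the support they need, from a generic approach to a breakthrough or tailored one. The section on the first level recalls that in earlier projects some hospitals began at once. Under the fourth level, stepping up depends on each hospital's own success.

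**The concern.** With one random hospital effect, two patients of the same hospital are equally correlated whether they are operated on in the same quarter or nine months apart. The design rests on a different picture: hospitals change at their own pace and, in the stepped arm, may receive different support in the same quarter. A hospital's deviation from the average can then shift from one quarter to the next.

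The stated model sets that shift to zero. Whatever exists of it goes into the patient-level residual, where it is spread over many patients and hardly raises the residual variance. The mean of a hospital-quarter nevertheless carries it in full. A test of change across quarters therefore uses an error term that is too small.

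At stake is the reading of the trends: whether outcomes improved from quarter to quarter, and whether the arms diverged. Such findings could be called significant too often, and they feed the judgement on which step levels are worth their cost.

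**Working it through.** **Inputs from the article**
- Seven hospitals per arm, so 14 in all; ICC 0.06; target 67 patients per hospital (Sample size).
- Four periods (Effect evaluation).
- Patients per hospital-quarter: 67/4 ≈ 17 from the target, or about 25 (Fourth implementation level).

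**Inputs assumed**
- The correlation of a hospital's effect between quarters, r. The article gives none; 0.9, 0.8 and 0.5 are shown.
- A lower ICC of 0.02. The Sample size section says its source reported lower ICCs for outcome than for process variables and that 0.06 is the highest applicable value, but it gives no lower figure.

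**The plan's own figure first.** For 50 % versus 70 %, two-sided 5 % and 80 % power:
- n per arm = [1.96·√(2·0.6·0.4) + 0.8416·√(0.25 + 0.21)]² / 0.2² = 93.
- Design effect = 1 + 59 × 0.06 = 4.54; 93 × 4.54 = 422; 422/60 = 7.04 hospitals per arm.
- Power at 7 × 60 is 79.8 %, and 60 × 1.11 = 66.6, i.e. 67.

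The sample size reproduces.

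**Error term for tests across quarters.** Set total variance to 1. Then
- patient variance σ² = 1 − ICC;
- stable hospital variance = ICC × r;
- hospital-by-period variance ω² = ICC × (1 − r).

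With m patients per hospital-quarter, the mean squares for period and for arm-by-period have null expectation σ² + mω². The stated model divides them by the pooled residual, with expectation

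[36(σ² + mω²) + 56(m − 1)σ²] / [36 + 56(m − 1)],

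where 36 = (14 − 2) × 3 and 56 = 14 × 4. The ratio is the inflation of the F statistic. For ICC 0.06, r = 0.8 and m = 25:
- ω² = 0.012, and σ² + mω² = 0.94 + 0.30 = 1.24;
- pooled residual = (36 × 1.24 + 1344 × 0.94)/1380 = 0.948;
- inflation = 1.24/0.948 = 1.31.

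The actual level of the 3-df test is then approximately P(F > c/inflation), where c is the 5 % critical value (2.61) and the degrees of freedom are 3 and 36 + 56(m − 1).

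| ICC | r | ω² | Inflation, m = 17 / 25 | Actual level, m = 17 / 25 |
|---|---|---|---|---|
| 0.06 | 1 | 0 | 1.00 / 1.00 | 5 % / 5 % |
| 0.06 | 0.9 | 0.006 | 1.10 / 1.15 | 6.9 % / 8.0 % |
| 0.06 | 0.8 | 0.012 | 1.21 / 1.31 | 9.1 % / 11.3 % |
| 0.06 | 0.5 | 0.030 | 1.51 / 1.76 | 15.9 % / 21.8 % |
| 0.02 | 0.9 | 0.002 | 1.03 / 1.05 | 5.6 % / 5.9 % |
| 0.02 | 0.8 | 0.004 | 1.07 / 1.10 | 6.2 % / 6.8 % |
| 0.02 | 0.5 | 0.010 | 1.17 / 1.25 | 8.2 % / 9.9 % |

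**Simulation** of the balanced linear model (20,000 trials per setting, ICC 0.06) agrees. Period / arm-by-period tests reject:
- r = 0.9: 6.7/6.7 % (m = 17) and 7.8/7.9 % (m = 25);
- r = 0.8: 9.2/9.0 % and 11.6/11.3 %;
- r = 0.5: 15.9/15.9 % and 22.2/22.0 %.

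Tested against the hospital-by-period mean square on 36 df, both return to about 5 %.

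**What is not affected.** Across all simulated settings, which also include m = 15 and ICC 0.02:
- the year-long arm effect on 12 between-hospital df rejects 4.6–5.4 %, because the hospital intercept absorbs the average of the quarter deviations;
- a final-quarter arm comparison fitted on its own, using hospital means, rejects 4.5–5.2 %;
- the same contrast taken from the pooled model with 12 df rejects 3.2–6.8 %.

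**The case against.** The strongest case on the other side is about relevance and size.

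- **The main question is untouched.** This stands. The declared main goal is the arm comparison over all patients of the year, and its error rate stays near 5 %.
- **The affected tests are hardly announced.** Entering period as a factor may be meant only as adjustment, no arm-by-period term is named, and the trend analyses are said to describe. This largely stands. But the article also sets a significance threshold without exempting the trend analyses and uses the three-monthly results to judge step levels, so p-values across quarters are a likely product of this model.
- **The ICC of 0.06 is the highest applicable value.** It is conservative for sample size but gives the largest effect here. Length of stay is an outcome variable, for which the article itself says ICCs are lower. This stands and is why ICC 0.02 is shown beside it.
- **The form of the variation is uncertain.** Support that varies by hospital and quarter exists only in the stepped arm, and different speeds may look more like diverging slopes than independent quarter effects. This stands, so the fix allows either term.
- **A condensed article may leave covariance detail to a fuller document.** This is fair for detail. The article does state one random effect together with a period factor, however, and that stated choice is what is examined.

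A reader might infer that every p-value for an arm difference over time is too small, including the planned three-monthly comparisons. The documents do not support that. The article does not say how those comparisons are fitted; done separately within each quarter with a random hospital effect they are valid, and as single-quarter contrasts from the pooled model with 12 df they are only slightly off.

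**Conclusion.** The point holds in a limited form. The stated model has no term for hospital-by-quarter variation, which the article's own premise makes plausible. If such variation exists, tests of change across quarters in the pooled model are too liberal.

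The planning ICC gives about 7–8 %, 9–12 % or 16–22 % instead of 5 % at between-quarter correlation 0.9, 0.8 or 0.5. An assumed ICC of 0.02 gives about 6 %, 6–7 % or 8–10 %. The largest figures need the highest ICC together with the lowest correlation shown, and the article supports neither for length of stay.

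The results rest on a balanced linear model with equal hospital-by-period variance in both arms. The logistic model shares the mechanism, but its percentages may differ. Severity is minor: secondary analyses only, with no consequence for the main arm comparison.

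**What to change.** In Data analysis, Effect evaluation, add a random hospital-by-period effect nested in hospital, or random hospital time slopes, to the models used for inference on period, trend or arm-by-period contrasts. State small-sample degrees of freedom, since only 14 hospitals are planned. Alternatively, label the analyses over time as descriptive and report them without p-values. Also say whether the three-monthly arm comparisons are fitted separately per quarter or taken from the pooled model.

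The cost is one variance term and wider intervals for the time trends. The year-long arm estimate is essentially unchanged.
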